#### **7.2.2 Serious adverse events (SAEs)**

A serious adverse event is any untoward medical occurrence or effect that at any dose:

- results in death;
- is life threatening (at the time of the event);
- requires hospitalisation or prolongation of existing inpatients' hospitalisation;
- results in persistent or significant disability or incapacity;
- is a congenital anomaly or birth defect;
- Any other important medical event that may not result in death, be life threatening, or require hospitalization, may be considered a serious adverse experience when, based upon appropriate medical judgement, the event may jeopardize the subject or may require an intervention to prevent one of the outcomes listed above.

All SAEs will be reported by the local investigator to the sponsor as soon as possible, by using the form designed for this purpose, which will be available on the study website.,

The sponsor will report the SAEs through the web portal *ToetsingOnline* to the accredited METC that approved the protocol, within 15 days after the sponsor has first knowledge of the serious adverse events.

SAEs that result in death or are life threatening will be reported expedited. The expedited reporting will occur not later than 7 days after the responsible investigator has first knowledge of the adverse event. This is for a preliminary report with another 8 days for completion of the report.

### **7.3 Follow-up of adverse events**

All AEs will be followed until they have abated, or until a stable situation has been reached. Depending on the event, follow up may require additional tests or medical procedures as indicated, and/or referral to the general physician or a medical specialist. SAEs need to be reported till end of study within the Netherlands, as defined in the protocol

### **7.4 Data Safety Monitoring Board (DSMB)**

An independent Data Safety Monitoring Board (DSMB) will be asked to monitor the progress of the study and the safety of its participants. The DSMB will include: prof. dr. [name], prof. dr. [name], dr. [name], dr. [name] and dr. [name]. The DSMB will meet as required to review any expected adverse events and may ask to review outcomes or other data that may have an impact on the trial.

Given the low risk of serious adverse events, no interim analysis will be planned. Every 10 SAEs will be reported to the DSMB by the sponsor.

The advice of the DSMB will only be sent to the sponsor of the study. The sponsor will decide if the advice of the DSMB will be implemented. And will subsequently update the reviewing METC on this advice including a note to substantiate why (part of) the advice of the DSMB will not be followed).

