## SUMMARY

**Rationale:** Hysteroscopic myomectomies are performed in the majority of Dutch hospitals. The number of procedures for submucosal type 0 or I myomas between 1-3 cm performed in the operating room is estimated to be 3000 per year. Hysteroscopic myomectomy is currently performed in daycare under general anesthesia. A considerable cost reduction is expected when procedural sedation (PSA) is applied. The major contributing factors to the cost reduction are the shift from surgery in an operating theatre to an office-based setting, shorter hospital stay and outpatient care versus day care. We expect higher patient satisfaction, as hospital stay is shorter and side effects such as nausea are reduced. However, both safety and effectiveness – including the necessity for re-intervention due to incomplete resection – have not yet been fully evaluated.

**Objective:** Is hysteroscopic resection of submucous myomas under procedural sedation with propofol (PSA) in an outpatient setting a cost-effective alternative for hysteroscopic myomectomy performed under general anesthesia in the operation room?

**Study design:** non-inferiority, multicenter RCT, with a cost effectiveness analysis (CEA) alongside it.

**Study population:** patients with submucosal type 0 or I myomas (FIGO (PALM COEIN)) with a maximum diameter of 3 cm. We use a non-inferiority design: based on estimated risk of 2,5% incomplete resections in both groups, with an non-inferiority upper limit of 10%, 205 women are needed.

**Intervention:** hysteroscopic resection of submucous myomas under procedural sedation with propofol, compared to general anesthesia

**Main study parameters/endpoints:** 1) complete resection 2) costs, pain, menstrual blood loss (PBAC score), , quality of life, return to daily activities/work, hospitalization, (post)operative complications, re-interventions.

**Nature and extent of the burden and risks associated with participation, benefit and group relatedness:** Patients participating in this study are requested to complete a questionnaire at baseline, after 24 hours, 2 weeks, 8 weeks, 6 months and 12 months after the procedure. At 6 weeks after the procedure patients are asked to visit the outpatient department for a transvaginal ultrasound to assess the completeness of resection. This visit is part of the current usual care.

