## **Relevance**

**THE INTERVENTION TO BE INVESTIGATED:** Hysteroscopic myomectomy for symptomatic type 0 or I submucosal myomas in an outpatient setting using procedural sedation with propofol compared to hysteroscopic myomectomy in an inpatient clinical setting using general anesthesia. According to the guidelines from the Health Care Inspectorate (IGZ) and Dutch Institute for Healthcare Improvement (CBO) procedural sedation is administered by a qualified sedation practitioner with standard monitoring.

**EXISTING EVIDENCE OF EFFECTIVENESS:** Due to proved safety, higher patient satisfaction, shorter procedure time and faster recovery the use of propofol in sedation practice has increased [11-12; 20]. Analogue to the successful shift of diagnostic procedures to an office-based setting [21-22], hysteroscopic myomectomies can be moved away from the operating theatre when adequate sedation and analgesia is secured. In a systematic review we found two studies evaluating feasibility and patient satisfaction with gynaecological surgery under procedural sedation [23-24]. From these studies, sedation with propofol/alfentanil seems to be feasible for endometrial balloon ablation and prolaps surgery.

In a second systematic review we evaluated the outcome of hysteroscopic resection of type 0 and type 1 myomas. The results of hysteroscopic removal of type 0/1 are very good with complete removal up to 100% and successful reduction of menstrual bleeding. The risk of complications is low (3,2% in a prospective bipolar resection trial of 449 patients) [25].

In summary, the systematic review evidence suggests that 1. procedural sedation anesthesia is feasible and well-tolerated in gynaecological surgery; and 2. hysteroscopic myomectomy is a safe and technically successful procedure. However, there are no randomised efficacy data.

**INNOVATIVE CHARACTER:** The proposed RCT is the first trial comparing the use of PSA in hysteroscopic myomectomy compared with the current standard hysteroscopic myomectomy in an inpatient setting under general anesthesia.

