### **4.4 Sample size calculation**

The study is designed as a non-inferiority study, in which we want to investigate if hysteroscopic myomectomy under procedural sedation with propofol is non-inferior to the same surgical procedure under general anesthesia. With 205 women randomized we have 90% power to demonstrate non-inferiority, based on an estimated 2,5% incomplete resections in both groups, with an non-inferiority upper limit of 10% incomplete resections defined as non-inferior (i.e. a delta of 7.5%), an alpha of 0.025 and a drop-out rate of 10%.

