#### **8.4 Interim analysis**

Given the low risk of adverse events, an interim analysis will not be planned.

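### The DSMB's only defined data flow, a report every 10 SAEs over both arms, is badly matched to a 205-woman trial in which the protocol itself expects few SAEs

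*Protocol*

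**What the plan says.** Protocol section 7.4 asks an independent DSMB to follow trial progress and participant safety. On meetings and access it says: "The DSMB will meet as required to review any expected adverse events and may ask to review outcomes or other data". On what the sponsor sends, the only rule is "Every 10 SAEs will be reported to the DSMB by the sponsor". The section gives no meeting frequency, accrual or calendar schedule, or threshold by arm.

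Section 7.4 also states "Given the low risk of serious adverse events, no interim analysis will be planned", and section 8.4 repeats the decision: "Given the low risk of adverse events, an interim analysis will not be planned".

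The protocol states no expected SAE rate. Its one event rate is in section 1, under the existing evidence of effectiveness: "The risk of complications is low (3,2% in a prospective bipolar resection trial of 449 patients". In the sentence that opens "However, both safety and effectiveness", the Summary concedes that neither has so far been completely assessed for the sedation approach.

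Other safety provisions are in section 7.2.2 (SAEs to the METC within 15 days, fatal or life-threatening ones within 7), section 7.1 (suspension pending METC review) and section 10.3 (SAEs in the yearly METC report).

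**The concern.** A count-based trigger is useful only if the count is likely to be reached while the board can still act. Here the threshold is a total over the whole trial. The reason given for light monitoring, that serious events are rare, is also the reason the threshold is hard to reach. The rarer SAEs are, the less the DSMB is sent.

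A count over both arms also ignores how the events are divided. Safety under outpatient sedation is an open question of this trial, and the signal of interest is an excess in one arm. Up to nine SAEs could fall almost entirely in the sedation arm without the rule sending anything to the board. Comparing arms on accumulating data is normally the DSMB's task, and no other body in the protocol is given it.

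**Working it through.** **Inputs.** N = 205 (section 4.4). Trigger = 10 SAEs in total (section 7.4). Complication rate 3.2% of 449 patients (section 1), used as a proxy because no SAE rate is stated. Assumptions: 1:1 allocation (not stated), about 103 women under sedation and 102 under general anesthesia; at most one SAE per woman, arising at the procedure.

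**Step 1: the plan's own figure.** Section 4.4 says "With 205 women randomized we have 90% power to demonstrate non-inferiority", "based on an estimated 2,5% incomplete resections in both groups", with a margin of 7.5 points, alpha 0.025 (read as one-sided) and 10% drop-out. Per arm,

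n = (1.960 + 1.282)² × 2 × 0.025 × 0.975 / 0.075² = 91.1, rounded up to 92.

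Two arms give 184, and 184 / 0.90 = 204.4, rounded up to 205. The sample size reproduces and is not in question.

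**Step 2: expected events at the proxy rate.** 205 × 0.032 = 6.56, fewer than one batch of 10.

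**Step 3: chance of reaching the trigger.** P(X ≥ 10) with X ~ Binomial(n, p), at n = 103 (half accrual), 154 (three quarters) and 205 (end). The last column is the negative binomial median of the patient number at the tenth SAE.

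| Assumed SAE rate | Expected in 205 | By half accrual | By 75% accrual | By end | Median patient at 10th SAE |
|---|---|---|---|---|---|
| 2% | 4.1 | <0.1% | 0.1% | 0.9% | 484 |
| 3.2% | 6.6 | 0.2% | 2.7% | 12% | 302 |
| 4% | 8.2 | 0.8% | 9.1% | 31% | 242 |
| 5% | 10.3 | 3.4% | 24% | 58% | 194 |
| 6% | 12.3 | 9.0% | 45% | 79% | 161 |
| 8% | 16.4 | 31% | 80% | 97% | 121 |

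A median above 205 means that the trigger is more likely than not never met. An even chance of ever meeting it needs an overall rate of about 4.7%, and an 80% chance about 6.1%.

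**Step 4: uncertainty in the proxy.** 3.2% of 449 is about 14 patients, with an exact 95% interval of 1.7% to 5.2%. Over that interval the chance of ever reaching 10 runs from 0.3% to 62%.

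**Step 5: a real excess under sedation.** With 3.2% under general anesthesia, the two binomial counts are added.

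| Sedation rate | By half accrual | By 75% accrual | By end |
|---|---|---|---|
| 6.4% (doubled) | 2.7% | 21% | 53% |
| 9.6% (tripled) | 12% | 53% | 86% |

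**Step 6: imbalances below the threshold.** With 103 v 102 women, 9 v 0 has a two-sided Fisher p of 0.003 and 8 v 1 a p of 0.035. Both total nine, so neither triggers a report. A 6 v 1 split (p = 0.12) would be weaker evidence.

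**The case against.** A reader might infer that safety oversight of outpatient sedation is merely nominal. The documents do not support that. SAEs go to the METC within 15 days, and within 7 if fatal or life-threatening (section 7.2.2). Section 7.1 suspends the study if the disadvantages of participation appear significantly greater than foreseen. Section 10.3 adds a yearly account, and section 7.4 lets the DSMB meet as needed and request data. The batch rule sets a minimum for what the sponsor sends and does not limit what the board may see. Nor does section 7.4 say that the report itself is pooled or masked; only the count that triggers it is a total.

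A reader might also infer that the trigger will probably never be met, or only once nearly everyone has been treated. That depends on a rate the protocol does not give. The 3.2% covers all complications in an outside resection series, not SAEs under sedation. SAEs here include any hospitalisation until end of study (sections 7.2.2 and 7.3), and a woman may have more than one. The true rate could be lower or higher. At 5% the trigger is more likely than not met; at 8% the tenth SAE comes at about patient 121 of 205.

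It can also be said that light monitoring is reasoned: section 7.4 calls the SAE risk low, and section 9.3 describes both anesthetic approaches as daily practice.

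These points rule out the stronger readings. They do not rescue the rule. METC reporting goes case by case and schedules no comparison of arms. The right to ask for data does not tell the board when to ask. The Clinical Evaluation Committee in section 8.1 categorises events but has no monitoring role. A low SAE risk makes a threshold of 10 harder to reach, so the rule fits least well where the protocol's premise is right.

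**Conclusion.** The point holds in a limited form. The one data flow to the DSMB that the protocol defines is poorly matched to 205 women and to its own expectation of few SAEs. At the proxy rate of 3.2% it is met with probability 12% by trial end and 0.2% by half accrual.

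Whether it is ever met depends on the unstated SAE rate: 1% at a rate of 2%, 97% at 8%. That it is unlikely by mid-trial is more robust, since the chance by half accrual is still 31% at 8%. These figures assume at most one SAE per woman, at the procedure. Several per woman would bring the trigger forward; SAEs arising later in follow-up would delay it. The by-arm results also assume 1:1 allocation.

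This is a stated rule that performs badly, not a detail left to another document. It should be changed, but it does not show that participants are without independent protection.

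**What to change.** In section 7.4, replace or supplement the 10-SAE trigger with cumulative listings, by arm, of SAEs and of procedural and sedation complications, sent to the DSMB at fixed accrual or calendar points. Every 50 women or every six months would do; the exact interval matters less than its being fixed in advance. Copy each fatal or life-threatening SAE to the DSMB when it is expedited to the METC. Stating the expected SAE rate would let the board judge what it sees.

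The cost is about four short listings (205 / 50 ≈ 4; or 24 months of inclusion / 6 = 4) from data already collected. No efficacy interim is needed, so sections 7.4 and 8.4 can keep that decision, and there is no alpha cost.

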## 8. STATISTICAL ANALYSIS

### 8.1 Data analysis and presentation/synthesis

Primary analysis will be by intention-to-treat. We will also perform a per protocol analysis, given the non-inferiority design of the study, where crossover between the groups will increase the chances of concluding non-inferiority, if in reality the treatment is not-inferior. We will present the percentage of complete resections at 6 weeks in both groups, with according relative risks and 95% confidence interval. Differences will be tested with the chi-square test, or, if the expected cell count is low using the Fisher exact test. We will also calculate the relative risk, adjusted for center where the procedure has been performed. Complications during and after surgery, and re-interventions will be categorized and evaluated by a Clinical Evaluation Committee, independent and blinded for the type of surgery performed (where possible). Average pain intensity during the procedure as well as the highest pain intensity during the procedure will be reported as means with SD, risk differences between both groups will be calculated with according 95% confidence interval. Time to recovery and pain will be visualized in a graph, and analyzed using a mixed model, that can take into account repeated measures in the same woman over time. The quality of life and PBAC scores will be analyzed according the developed algorithms. We will perform a subgroup analysis for myoma size (<2 cm versus  $\geq 2$  cm) and for parity (nulliparous versus multiparous women).

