## 2. OBJECTIVES

**Primary Objective:** To demonstrate non-inferiority of complete hysteroscopic resection of submucous myomas under procedural sedation with propofol compared to hysteroscopic resection under general anesthesia.

**Secondary Objective(s):** To compare the cost effectiveness, pain, menstrual blood loss (PBAC score), quality of life, return to daily activities/work, hospitalization, (post)operative complications, re-interventions for hysteroscopic resection of submucous myomas under procedural sedation with propofol and for resection under general anesthesia.

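### Section 8.1 makes intention-to-treat the only primary analysis despite its own crossover warning, gives per protocol no stated part in the conclusion, misstates the reason for it, and ties neither to the 7.5-point margin

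*Protocol*

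**What the plan says.** The primary objective (Protocol, section 2) is "To demonstrate non-inferiority of complete hysteroscopic resection of submucous myomas under procedural sedation with propofol compared to hysteroscopic resection under general anesthesia". Section 4.4 sizes the trial "based on an estimated 2,5% incomplete resections in both groups", with a "non-inferiority upper limit of 10% incomplete resections defined as non-inferior (i.e. a delta of 7.5" percentage points), alpha 0.025, 90% power and 10% drop-out, giving 205 women.

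Section 8.1 then sets the analysis: "Primary analysis will be by intention-to-treat. We will also perform a per protocol analysis, given the non-inferiority design of the study", and gives as the reason that "crossover between the groups will increase the chances of concluding non-inferiority, if in reality the treatment is not-inferior". The rest of its plan for the primary endpoint is the percentage of complete resections per arm, relative risks with 95% confidence intervals, a chi-square or Fisher test of the difference, and a centre-adjusted relative risk. The 7.5-point margin does not appear in section 8.1, the per-protocol set is not described, and nothing says how the two analyses combine. Section 6.2 states that patients and staff know the allocation.

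**The concern.** Three features of section 8.1 work against each other.

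- It identifies crossover as pushing the result towards the claim the trial hopes to make, and then names as sole primary the analysis most exposed to it. The analysis added as a safeguard has no stated way to affect the conclusion.
- The reason is worded backwards. Concluding non-inferiority for a treatment that is not inferior is the right answer. The hazard arises when sedation is in reality inferior. Read literally, the sentence gives no reason for a per-protocol analysis.
- The planned statistics are a relative risk and a test of difference. Neither asks whether the excess of incomplete resections is below 7.5 points, so neither analysis as described answers the primary objective.

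At stake is a non-inferiority claim that intention-to-treat supports and per protocol does not, with no rule agreed in advance. Section 1 says the professional society has agreed to adjust its guideline once (cost-)effectiveness is proven, so such a claim would reach practice.

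**Working it through.** **Reproducing the plan's figure.** Inputs from section 4.4: 2.5% incomplete in both arms, margin 0.075, 90% power, alpha 0.025 taken as one-sided. Equal allocation is assumed because no ratio is stated.

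n per arm = (1.960 + 1.282)² × 2 × 0.025 × 0.975 / 0.075² = 91.06, so 92. Total evaluable 184; 184 / 0.90 = 204.4, so 205. The stated size reproduces, which supports a one-sided 0.025 test, equivalent to a two-sided 95% interval.

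**Effect of crossover on intention-to-treat.** The protocol gives no crossover rate, so 0 to 20% is assumed, from sedation to general anesthesia and unrelated to outcome. True incomplete rates are set at the margin: 10% under sedation, 2.5% under general anesthesia. With crossover share c, the sedation-arm risk is (1 − c) × 10% + c × 2.5%, so the intention-to-treat difference is 7.5 × (1 − c) points: 7.125 at 5%, 6.75 at 10% and 6.0 at 20%. Per protocol drops the crossovers.

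The table gives the probability of passing with 92 per arm, where passing means an upper 95% limit below 7.5 points. The interval is Newcombe's, a score-type interval; the Farrington-Manning score test gives the same intention-to-treat figures.

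| Crossover | Intention-to-treat passes | Both pass | Intention-to-treat passes, per protocol fails |
|---|---|---|---|
| 0% | 2.1% | 2.1% | 0% |
| 5% | 2.7% | 1.9% | 0.7% |
| 10% | 3.3% | 1.9% | 1.5% |
| 20% | 5.2% | 1.8% | 3.4% |

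The normal approximation for intention-to-treat gives 2.5%, 3.2%, 4.1% and 6.6%. A Wald interval passes in 4.5% of trials even without crossover, rising to 5.6%, 6.9% and 10.4%; requiring both then gives 4.1%, 4.3% and 4.8%. The choice of interval therefore matters as well.

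**If conversion follows difficulty.** Assume 25% of cases are difficult, with incomplete rates for difficult and easy cases of 31% and 3% under sedation and 5.5% and 1.5% under general anesthesia. The averages are again 0.25 × 31 + 0.75 × 3 = 10% and 0.25 × 5.5 + 0.75 × 1.5 = 2.5%. Only difficult cases convert. At 10% conversion, the sedation women left in the per-protocol set have risk (0.15 × 31 + 0.75 × 3) / 0.90 = 7.7%, a difference of about 5.2 points, so per protocol is also flattered. At 5, 10 and 20% conversion, intention-to-treat passes in about 4.6%, 9.4% and 32% of trials, and both pass in about 3.5%, 6.5% and 23%.

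**Power cost, true rates 2.5% in both arms, random crossover.**

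| Crossover | Both pass, Newcombe | Both pass, Wald |
|---|---|---|
| 0% (same as intention-to-treat alone) | 73.5% | 89% |
| 5% | 70% | 86% |
| 10% | 67% | 85% |
| 20% | 60% | 82% |

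The planning formula gives 90.3% at 92 per arm. The Newcombe figure is lower because events are few.

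**The case against.** The best defence is that the protocol is silent on the role of per protocol and does not deny it one. A rule for discordant results and a definition of the per-protocol set are commonly left to a statistical analysis plan, which is not shown here. Intention-to-treat as primary with per protocol in support is an accepted arrangement. This stands in part: a reader might infer that the protocol lets intention-to-treat decide alone and would uphold a claim that per protocol contradicts, but section 8.1 does not say so. What it does state can still be faulted: a single primary analysis, a warning about that analysis, a reversed reason, and statistics that do not address the margin. A later plan making per protocol co-decisive would have to depart from this text.

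A second objection is that the word false depends on the question. At 20% crossover the difference between strategies is 6.0 points, inside the margin. For a strategy of starting with sedation and converting where needed, passing is then correct. This stands. A reader might take 5.2% as a doubled type I error, but it is an error only if the target is the effect of sedation itself.

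Third, per protocol is itself biased when conversions are linked to difficult resections. This also stands, and is why it should accompany intention-to-treat and not replace it. A reader might infer from the random-crossover table that requiring both analyses keeps the error below 2.5%; the second scenario shows that it need not.

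That the intended word is recoverable from context is true, but the sentence still needs correcting.

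**Conclusion.** The concern holds as a defect in what section 8.1 fixes: its primary analysis, its stated reason and its test statistics do not fit together or with section 4.4. The sample size is not in dispute.

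The size of the problem depends on a crossover rate the protocol does not give. Under random one-way crossover with sedation at the margin, the excess is negligible at about 5% (2.7% against a nominal 2.5%), modest at 10% (3.3%) and clear at 20% (5.2%). It can be much larger if conversion follows difficulty, though that scenario rests on invented strata and shows direction more than size. Requiring both analyses reduces the error in every case examined and can never be more lenient than intention-to-treat alone. It is an improvement and not a guarantee.

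**What to change.** Replace the analysis-set sentences in section 8.1 with text to this effect:

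*Non-inferiority will be concluded only if the upper limit of the two-sided 95% confidence interval for the risk difference in incomplete resection (sedation minus general anesthesia) is below 7.5 percentage points in both the intention-to-treat and the per-protocol analysis. If only one analysis meets this, the result will be reported as inconclusive. The per-protocol analysis is included because crossover makes a non-inferiority conclusion more likely if in reality the treatment is inferior.*

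In the same edit, define the per-protocol set, including how women who convert from sedation to general anesthesia are counted, and name the interval method. Report the number of conversions so that readers can judge how far either analysis may be biased. Relative risks can remain as description.

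The change takes a few sentences. Both analyses are already planned, so no new data are needed, and because both must succeed no alpha adjustment is required. The real cost is power: with equal arms, a loss of about 4, 7 and 14 percentage points at 5, 10 and 20% crossover with the score-type interval, or about 3, 4 and 7 with Wald. If substantial crossover is expected, the 205 should be reconsidered, since it allows for drop-out but not for this rule.

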## **6. METHODS**

### **6.1 Study parameters/endpoints**

#### **6.1.1 Main study parameter/endpoint**

Primary outcome will be the percentage of complete resections, based on ultrasonography 6 weeks postoperatively by an independent gynaecologist or ultrasonographer blinded for the surgery outcome. This ultrasonography should be conducted in the follicular phase (first 14 days) of the menstrual cycle. A complete resection means that there are no signs of an intracavitary remaining of the myoma resected during hysteroscopic myomectomy on the transvaginal ultrasound.

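### Section 8.1 plans a test of no difference and a relative risk for the primary endpoint, and compares no confidence interval with the 7.5-point non-inferiority margin

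*Protocol*

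**What the plan says.** Protocol section 2 gives the primary objective: "To demonstrate non-inferiority of complete hysteroscopic resection of submucous myomas under procedural sedation with propofol compared to hysteroscopic resection under general anesthesia". Section 6.1.1 makes the endpoint binary: "Primary outcome will be the percentage of complete resections, based on ultrasonography 6 weeks postoperatively".

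Section 4.4 sizes the trial for 90% power at alpha 0.025 with 10% drop-out, "based on an estimated 2,5% incomplete resections in both groups", and sets the margin as a "non-inferiority upper limit of 10% incomplete resections defined as non-inferior (i.e. a delta of 7.5" percent.

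Section 8.1 makes intention-to-treat primary and adds a per-protocol analysis. For the primary endpoint it plans the percentages of complete resection, relative risks with 95% confidence intervals, a centre-adjusted relative risk, and this test: "Differences will be tested with the chi-square test, or, if the expected cell count is low using the Fisher exact test". The margin does not appear in section 8.1. The only risk difference with an interval in that section stands in the sentence on pain. The reason given for the per-protocol analysis is a situation "where crossover between the groups will increase the chances of concluding non-inferiority, if in reality the treatment is not-inferior".

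**The concern.** A chi-square or Fisher test takes equal proportions as its null hypothesis. Non-inferiority takes as its null that sedation is worse by at least the margin, and it is shown by rejecting that. The two can disagree in either direction, and with few events a non-significant test of equality says little about the margin. The effect measure is also on another scale: the margin is an absolute difference and the planned estimate is a ratio, for which no margin is stated.

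This is more than detail left for a statistical analysis plan. The protocol names a test, and it is the wrong kind for the objective. A later plan must either inherit the test or depart from the protocol. What is at stake is the trial's central conclusion.

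The crossover sentence adds to this. Crossover makes the arms look alike, and the danger in a non-inferiority trial is a false claim when the treatment is in truth inferior. The sentence as written describes the opposite case. The protocol also does not say what follows if the per-protocol and intention-to-treat results disagree.

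**Working it through.** **Inputs.** From section 4.4: 2.5% incomplete in both arms, margin 7.5 points, alpha 0.025, power 90%, drop-out 10%, 205 randomised. Assumed: 1:1 allocation and a one-sided alpha, neither of which is stated.

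**Step 1: reproduce 205.** For a margin test on the risk difference,

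n per arm = (z₀.₉₇₅ + z₀.₉₀)² × [p₁(1−p₁) + p₂(1−p₂)] / δ²
= (1.960 + 1.282)² × (2 × 0.025 × 0.975) / 0.075² = 91.06, rounded up to 92.

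Total 184; 184 / 0.90 = 204.4, rounded up to 205. This is an exact match. By contrast, a two-sided 5% test of equality with 90% power to detect 2.5% versus 10% would need 217 per arm, or 483 after drop-out. The trial was therefore sized for a margin test on the risk difference, which section 8.1 does not contain.

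**Step 2: the named tests when sedation is exactly at the margin.** All pairs of binomial counts were enumerated at 92 per arm, with a true 10% versus 2.5% incomplete.

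| Rule | Probability |
|---|---|
| Chi-square (uncorrected) p ≥ 0.05 | 43.7% |
| Chi-square, with Fisher if an expected count is below 5 (assumed cut-off), p ≥ 0.05 | 47.0% |
| Fisher p ≥ 0.05 | 54.8% |
| Newcombe upper 95% limit below 7.5 points | 2.1% |
| Wald upper 95% limit below 7.5 points | 4.5% |

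The first three rows are false claims of non-inferiority only if non-significance is read as non-inferiority.

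**Step 3: one possible result.** With 8/92 incomplete under sedation and 2/92 under general anesthesia, the difference is 6/92 = 6.5 points. Fisher gives p = 0.10 and chi-square p = 0.051, so neither is significant. The Newcombe 95% interval is −0.3 to 14.2 points, and its upper limit is nearly twice the margin.

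**Step 4: power of a margin rule at the planned size.** With a true 2.5% in both arms and 92 per arm:

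| Interval for the risk difference | Exact power | False claims at the margin |
|---|---|---|
| Wald | 89.1% | 4.5% |
| Newcombe | 73.6% | 2.1% |

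A score test gives the same two figures as Newcombe. Wald comes close to the stated 90% power, but its error exceeds 2.5%. Newcombe and score keep the error but lose about 16 points of power (90 − 74).

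**Step 5: the two expressions of the margin.** The 10% limit and the 7.5-point difference coincide only at a 2.5% control rate (2.5 + 7.5 = 10). At a 5% control rate the difference would allow 12.5%.

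**The case against.** The strongest reply is that the ingredients are present. Margin, alpha and power are fixed in section 4.4, and 205 follows from a margin test. The planned 95% level matches a one-sided 0.025, and a risk difference with its interval can be computed from the reported percentages. What is missing is a sentence tying the interval to the margin, and an analysis plan not at hand may contain it. This stands as a limit on the point: the data and the sample size can answer the objective. It does not remove the point, because section 8.1 prescribes a different test.

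A reader might infer more than the protocol supports:

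- **That the plan treats a non-significant test as success.** No section says so. The 44% to 55% figures are conditional on that misreading.
- **That the relative risk and the margin give opposite answers.** Section 8.1 plans the relative risk of complete resection. On that scale the margin corresponds to 0.90 / 0.975 = 0.923. With 2 incomplete in each arm the relative risk is 1.00 (0.958 to 1.044), which passes, as the risk difference does. Set against 0.923, the planned interval behaves like the Wald risk difference (89.1% power, 4.5% false claims). The fault is that no bound is stated.
- **That the protocol holds two rival margins.** Section 4.4 itself equates the 10% with the 7.5-point delta. It needs only to say which governs if the control rate is not 2.5%.
- **That crossover distorts the result by a known amount.** The protocol gives no crossover rate, so no size is claimed. The intent of the sentence is sound; its wording is not.

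**Conclusion.** The point holds, and it should be fixed before analysis because it concerns the trial's central inference. The objective, margin and sample size call for a risk difference judged against 7.5 points. Section 8.1 names a test of equality and a relative risk, and states no decision rule.

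If non-significance were taken as non-inferiority, the chance of passing a sedation arm exactly at the margin would be about 44% to 55%, depending on the test, against about 2% to 4.5% with a margin rule. These figures rest on 1:1 allocation, 92 evaluable women per arm, a two-sided 0.05 threshold for the tests of equality and, for the 47% figure, an expected-count cut-off of 5.

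It would go too far to say that the trial cannot answer its question. The defect lies in the written analysis, not in the data to be collected.

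**What to change.** In section 8.1, make the primary analysis the difference (sedation minus general anesthesia) in the proportion with incomplete resection at 6 weeks, with a two-sided 95% confidence interval by a named method. Conclude non-inferiority only if the upper limit is below 7.5 percentage points. Keep the relative risks and the chi-square or Fisher test as descriptive.

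In section 4.4, state that the 7.5-point difference governs and that 10% is only its value at a 2.5% control rate. Give the power for the chosen interval. If Newcombe or a score interval is used, the stated 90% must be replaced by about 74% at 92 evaluable per arm, or the sample size reconsidered. If Wald is used, state its error of about 4.5% at the margin.

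Correct the crossover sentence so that it refers to a treatment that is in reality inferior. State the role of the per-protocol result in the conclusion, for example that both sets must meet the criterion; such a requirement cannot raise the power.

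The decision rule and the corrections cost wording only, with no new data. The choice of interval carries a real cost in either power or error, and the sponsor should make it knowingly.
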